### Data analysis

As JtD is a pragmatic parallel group randomised trial, with a usual care (control) arm, data will be reported and presented according to a revised CONSORT statement.^44^ Statistical analysis will be performed on an ITT basis. All exploratory tests will be two-tailed with alpha=0.05. Baseline demographics and quality of life data will be described and summarised overall and by treatment group.

The primary analysis will compare mean patient reported DEMQOL scores at 8 months postrandomisation between the intervention (JtD) arm and control arms using a mixed effects linear regression model adjusted for DEMQOL baseline score and site and allowing for the clustering of the outcome by the JtD intervention.^45–47^ The trial is a partially nested design with comparison of a group therapy (JtD) with individual therapy with clustering in one (intervention) arm. Each person with dementia in the control group (unclustered arm) will be treated as a cluster (singleton) of size one. The cluster indicator will be treated as a random effect. A stratification variable used for randomisation (site) will be included as a fixed factor.^48^ A partially clustered mixed effects linear regression model with homoscedastic errors as well as a heteroscedasticity mixed effects linear regression model will also be considered to account for potential differential variability of outcomes between the two treatment groups. A 95% CI for the mean difference in DEMQOL scores between the intervention and control groups will be calculated together with the associated p value. A further adjusted analysis may also be performed depending on the observed degree of imbalance in baseline covariates (which are of potential prognostic importance) again using a mixed effects linear regression model. Additional covariates (of potential prognostic importance) include other baseline variables, such as age, gender, PHQ-9 and GAD-7. In the event that there are more than 10 couples (20 participants) living under the same roof from different households in the study, then the primary and secondary analyses will be changed to take into account the hierarchical or clustered nature of the data. A multilevel mixed effects model will be used; the random effects will be JtD intervention groups (top level) and couple/singles (lower level). Individual participants who are not part of a couple will be treated as clusters of size one.

Participants will be followed up for up to 12 months postrandomisation. Mean DEMQOL scores at 12 months follow-up will be compared as described for the primary outcome above.

For the primary outcome, the DEMQOL score at 8 months follow-up, missing data will be imputed through a variety of methods including: regression and multiple imputation as part of a sensitivity analysis.

We will complement the ITT analysis of the primary outcome with a complier average causal effects analysis as a secondary analysis alongside the primary ITT analysis. Compliance will be defined as a binary variable with participants who attend at least 10 of the 16 JtD sessions (both individual and group sessions combined) regarded as being compliant.

There are no planned interim statistical analyses or formal stopping rules in relation to efficacy.

In terms of missing data, the primary analysis will be performed based on participants with available 8 month primary outcome data. Sensitivity analysis on the primary outcome will include multiple imputation using chained equations and regression imputation.

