### Outcome measures

Outcomes were identified through a feasibility study which identified appropriate measures and tested their application.^22^ The burden of questionnaires was found to be acceptable.

The primary outcome is the Dementia Related Quality of Life (DEMQOL)^30 31^ measure at 8 months postrandomisation.

The secondary outcomes are:

European Quality of Life-5 Dimensions, 5 level version (EQ-5D-5L).^32 33^
Patient Health Questionnaire-9 (PHQ-9).^34 35^
Generalised Anxiety Disorder-7 (GAD-7).^36^
General Self-Efficacy Scale (GSE).^37^
Diener’s Flourishing Scale (DFS).^38^
Self-Management Ability Scale (SMAS).^39^
Instrumental Activities of Daily Living (IADL).^40^
Health and Social Care Resource Use Questionnaire (HSCRU).^22^
Sense of Competency Questionnaire (SCQ).^41 42^

See table 1 for further information on who completes which measures in the study. The outcome measures used were selected to measure the following key components of the intervention: mental well-being or mood (DEMQOL, PHQ-9, GAD-7); building relationships and a sense of connectedness (DFS, SMAS); self-management (SMAS); belief that life is meaningful despite dementia (DEMQOL, GSE, DFS, SMAS) and Instrumental Activities of Daily Living (IADL) and strategies to maintain cognitive functioning (IADL). Additionally, they also support analysis of the cost-effectiveness of the intervention (DEMQOL, EQ-5D-5L, HSCRU) and the participating supporters’ perceptions of competence (SCQ). Dementia-specific outcome measures are those recommended for use across Europe and are selected for self rather than proxy completion.^43^ Non-dementia-specific outcome measures were selected if there was no appropriate dementia-specific measure available.

**Table 1 T1:** Outcome measures and time-points for collection

Measure	Participant				Participating supporter	
	Eligibility and consent visit	Baseline due <2 months prior to the intervention start date	8 months due <2 weeks before and <8 weeks after the 8 month anniversary of randomisation	12 months due <2 weeks before and <8 weeks after the 12 month anniversary of randomisation, if within study timelines	Baseline same timings as participant baseline visit	8 months same timings as participant 8 month visit
Capacity assessment	**✓**					
Mini Mental State Examination	**✓**					
Eligibility checklist	**✓**				**✓**	
Baseline demographics	**✓**				**✓**	
DEMQOL		**✓**	**✓***	**✓**		
EQ-5D-5L		**✓**	**✓**	**✓**	**✓**	**✓**

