### Data collection

Data will be collected from all participants living with dementia at eligibility/consent, baseline, 8 and 12 months postrandomisation and from consented participating supporters at baseline and 8 months’ postrandomisation (see table 1). There is a reduced set of measures linked to the 12 month visit as we require limited further information on quality of life and health and social care resource use at that time-point; the key outcome point is at 8 months. The outcome measures will be interviewer-administered at face-to-face visits by blinded outcome assessors who have received training to deliver the measures to people living with dementia and their supporters. The follow-up outcome measures will be collected 2 weeks pre and 8 weeks post the date they are due. Participant retention will be promoted by regular communication with the participants and supporters through communication including newsletters and Christmas cards.

Visits to collect outcome data will be arranged with the participant by a researcher; in some cases, a participating supporter will assist with these arrangements. All visits will be conducted at a time and location most suitable for the participant. When we conduct the follow-ups, we will prioritise the importance of the measures in case the participant tires. We will offer a second visit if the participant is tired or otherwise unable to complete the assessments, which will be organised as soon as possible after the first. Participating supporters may not have the time or capacity to receive a face-to-face visit and follow-up outcome measures may therefore be collected from them over the telephone. Similarly, if a participant does not want a visit, a reduced set of outcome measures may be taken by telephone (prioritising collection of DEMQOL and telephone versions of HSCRU and EQ-5D-5L).

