#### Secondary outcome measures

Secondary outcomes at 8 and 12 months postrandomisation will be compared between the intervention and control groups using a mixed effects linear regression model as for the primary outcome. A 95% CI for the mean difference in this parameter between the treatment groups will also be calculated together with the associated p value.

Outcome measures for the participating supporters at 8 months will be compared between the intervention and control groups using a mixed effects linear regression model. The mean difference in outcome with associated 95% CI and p value will be presented for: (1) the baseline (specific to the secondary outcome) and site adjusted analysis and (2) adjusted analysis with additional covariates in addition to (1).

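### The 12-month comparisons of DEMQOL, EQ-5D-5L and IADL leave out the 8-month score already collected, which costs some precision and leaves them open to a mostly small bias

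*Protocol article*

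**What the plan says.** All references are to the protocol article.

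- **12-month DEMQOL (Data analysis):** "Mean DEMQOL scores at 12 months follow-up will be compared as described for the primary outcome above".
- **The model this refers to (Data analysis):** scores at one visit are compared "using a mixed effects linear regression model adjusted for DEMQOL baseline score and site and allowing for the clustering of the outcome by the JtD", so group membership in the JtD arm is allowed for. On the random part: "The cluster indicator will be treated as a random effect". No term links a participant's two follow-up scores.
- **Other outcomes (Secondary outcome measures):** the same kind of model is named here: "Secondary outcomes at 8 and 12 months postrandomisation will be compared between the intervention and control groups using a mixed effects linear regression model", again following the primary outcome. Table 1 shows that EQ-5D-5L and IADL, like DEMQOL, are collected at baseline, 8 and 12 months.
- **Missing data (Data analysis):** on the analysis set, "the primary analysis will be performed based on participants with available 8 month primary outcome data". On imputation, the text adds: "Sensitivity analysis on the primary outcome will include multiple imputation using chained equations and regression imputation". Both sentences concern the 8-month primary outcome. The clinical analysis states nothing equivalent for 12 months.
- **12-month visit (Table 1):** "12 months due <2 weeks before and <8 weeks after the 12 month anniversary of randomisation, if within study timelines".
- **Priority of the time points (Data collection):** "the key outcome point is at 8 months".

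**The concern.** A single-time-point model has no record for a person without a score at that visit. Unless the value is imputed, someone assessed at baseline and 8 months but not at 12 drops out of the 12-month contrast. Yet that person's 8-month score is the closest earlier measurement of the same outcome.

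Two features of the design make such people likely. The study-timelines condition in Table 1 can cut off the 12-month visit for late recruits. The sections on withdrawal and on loss of capacity also foresee people leaving during follow-up.

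Two things are at stake, both confined to a secondary time point. The confidence interval is wider than the collected data require. The arm contrast is also exposed to bias if reaching the 12-month visit depends on how the person was doing at 8 months, which the trial has recorded.

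**Working it through.** **The plan's own figures.** None is given for 12 months. The 8-month sample size reproduces. A two-sample t calculation for a 4-point difference, SD 11, 90% power and two-sided 5% gives 160 per arm. The design effect is 1 + (8 − 1) × 0.03 = 1.21, and 160 × 1.21 = 193.6, so 194. Then 194 / 0.8 = 242.5, so 243 per arm and 486 in total. The point below does not touch these.

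**Inputs.** SD 11, the 4-point effect and 388 people with 8-month data come from the Sample size section. The correlations, the share of 8-month attenders who miss 12 months (p) and the strength of outcome-dependent loss are not in the article and are assumed. The simulations leave out clustering.

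**Precision, by formula.** Let r be the 8-to-12-month correlation given baseline. With loss unrelated to outcome, the variance relative to complete data is:

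- separate 12-month model: 1 / (1 − p)
- joint model of both visits: r² + (1 − r²) / (1 − p)

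| p | r | Separate | Joint | SE cut by joint model | SE excess of separate model |
|---|---|---|---|---|---|
| 0.1 | 0.5 | 1.111 | 1.083 | 1.3% | 1.3% |
| 0.2 | 0.7 | 1.250 | 1.1275 | 5.0% | 5.3% |
| 0.3 | 0.8 | 1.429 | 1.154 | 10.1% | 11.2% |

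**Precision, by simulation.** This used 388 people, p from 0.1 to 0.4 and 8-to-12-month correlations of 0.6 to 0.8 before adjustment for baseline. The variance ratio (separate to joint) ran from 1.021 to 1.264. The square roots are 1.010 and 1.124, so the SE is 1% to 12% larger. In the middle case (20% missing, correlation 0.7) the SEs were 1.07 and 1.03.

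The formula's r is conditional on baseline and the simulation's is not. A baseline correlation of 0.6 at both visits turns 0.8 into (0.8 − 0.36) / 0.64 = 0.69. The corner p = 0.4 with a conditional r of 0.8 lies outside both sets and would give √(1.667 / 1.24) = 1.16.

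**Bias, same dependence in both arms.** If loss after 8 months depends on the 8-month score identically in both arms and there is no effect, selection shifts both arms equally and the difference is unbiased. The simulated bias was within about 0.02.

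With a true 4-point effect at both visits, controls have more low scorers to lose. The estimates below use 400,000 per arm and correlations of 0.6 (baseline–8 months), 0.55 (baseline–12) and 0.75 (8–12):

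| Log-odds of loss per SD lower at 8 months | 10% loss | 20% loss | 30% loss |
|---|---|---|---|
| 0.5 | 3.94 | 3.91 | 3.91 |
| 1.0 | 3.90 | 3.79 | 3.76 |
| 1.5 | 3.78 | 3.65 | 3.55 |

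The shortfall is therefore about 0.1 to 0.45 points (4 − 3.55 = 0.45, or 11%). In the last cell, loss is 34% in controls and 26% in JtD. The joint model gave 3.97 to 4.01 throughout.

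**Bias, dependence differing by arm.** With slopes of 0 to 1, 15–40% loss and 8-to-12-month correlations of 0.6 to 0.8, the bias ran from about 0.2 points (slope 0.5 in controls, 1 in JtD, 15% loss, 4-point effect: +0.22) to about 1.4 (slope 0 against 1, 40% loss, no effect: +1.42; reversed: −1.43). The joint model stayed within about 0.04 of the truth.

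**Scale.** With an SE of 1.07 the 95% interval has a half-width of 1.96 × 1.07 = 2.1 points. A shift of 0.45 is about a fifth of that (0.45 / 2.1 = 0.21). A shift of 1.4 is about two thirds (1.4 / 2.1 = 0.67).

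**The case against.** **Separate models by time point are standard, and missing-data detail for a secondary visit often sits in an analysis plan that is not shown.** This is fair for sensitivity analyses. The sentence restricting the analysis to available data names only 8 months, so its extension to 12 months is by cross-reference. What remains is a stated choice: the 12-month model is specified, and the 8-month score is not in it. The Health economics evaluation section does plan multiple imputation for EQ-5D-5L and DEMQOL-U, but for the economic analysis.

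**Much 12-month loss may be harmless.** A cut-off set by study timelines depends on when a person was randomised, and allocation is balanced within site. It costs precision but should cause little bias. The article also continues follow-up after withdrawal from the intervention, keeps people who lose capacity where they and the consultee agree, and offers telephone collection that gives DEMQOL priority. All of this stands, and it argues for the lower part of the bias range.

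**A reader might infer that the comparison is biased whenever worse scorers at 8 months fail to reach 12 months.** The calculation does not support that. The same dependence in both arms gives no bias without an effect and a small one with a 4-point effect. Larger bias needs a dependence that differs by arm. That is conceivable, since participants are unblinded and only one arm has an intervention to leave, but nothing in the article shows it.

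**A reader might also take 12 months as the only evidence that an effect lasts.** Table 1 places baseline less than 2 months before the intervention starts, and the groups run for 12 weeks. If randomisation follows baseline, delivery ends at about month 5, so the 8-month outcome already falls about 3 months later.

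**Conclusion.** The point holds as a cheap improvement to a secondary analysis. The separate 12-month models discard recorded information that bears directly on the missing values. Under the stated assumptions the cost is a standard error about 1–12% too large, near 5% in the middle of the range.

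The exposure to bias is real but conditional. It is about nil with no effect and the same dependence in both arms, about 0.1 to 0.45 points towards zero with a 4-point effect, and about 0.2 to 1.4 points in either direction only if the dependence differs by arm. A claim that a lasting effect would be made to look as if it faded goes further than these figures, given an interval half-width of about 2.1 points.

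Every correlation, loss rate and slope is an assumption.

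**What to change.** Leave the 8-month primary model unchanged. Take the 12-month contrasts for DEMQOL, EQ-5D-5L and IADL from a repeated-measures mixed model with the 8- and 12-month scores as joint responses. Its terms are arm, visit, arm-by-visit, baseline score, baseline-by-visit and site, with an unstructured within-person covariance and the JtD-group random effect. Everyone with at least one follow-up score then contributes. Keep the separate 12-month model as a supportive analysis. To count as prespecified, the change must be recorded before database lock, which the Study status section describes as approaching.

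It needs a sentence in the analysis section and no new data, visits or participants. The downside is a more complex secondary model: a within-person covariance has to be fitted alongside the partially nested group effect and, if they are used, heteroscedastic errors or a couple level. The joint model does not help people missing at both visits, and it does not correct for loss that depends on the unseen 12-month score.

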### Sample size

The primary outcome for the study is the mean DEMQOL score 8 months postrandomisation. Assuming a SD of 11 points for the DEMQOL, a mean difference of 4 or more points is clinically and practically important.^30^ The sample size has been calculated to have a 90% power of detecting this 4 point difference (equivalent to a standardised effect size of 0.36) in group mean scores at 8 months as being statistically significant at 5% (two sided) level. As the JtD intervention is a facilitator led intervention with a group component, the outcomes of the participants in the same group with the same facilitators may be clustered. With no adjustment for clustering by facilitator, the target sample size would be 160 per arm with a total sample size of 320. We have assumed an average cluster size of 8 people with dementia per facilitated group and an intracluster correlation of 0.03; this will inflate the sample size by a design effect of 1.21, to 194 per group (388 total sample size) with valid primary outcome data. Assuming at least a 20% loss to follow-up the target sample size for the trial is to randomise to 243 participants in each arm (n=486).

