The second is the risk that during the trial, people with dementia may lose the capacity to consent to continuing participation. As part of the consent process, people with dementia will be asked to nominate a person to act as a consultee we may contact in the event that they lose capacity during the trial. The consultee will be independent from the study and can be a relative, friend or medical professional. All researchers will be provided with guidance and local training on identifying and dealing with capacity issues identified before or during 8-month and 12-month follow-up visits. If at any point the participant indicates they do not wish to continue to take part in the trial, they will be withdrawn. If the person with dementia loses capacity during the trial, but indicates they wish to remain in the study, the consultee will be asked to make a judgement, based on their existing and pre-existing knowledge of the person with dementia, about whether they would want to continue participation or not. If the consultee advises that the participant would wish to be withdrawn, the researchers will withdraw them from the study. If the consultee advises that the participant would wish to stay taking part, even though they lack capacity, every effort will be made to accommodate this, for example, by reducing the number of outcome measures or using prompts or other means to help the participant complete the measures. We will record information about the activation of the consultee pathway on the trial.

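### Regression imputation, named as a separate sensitivity analysis, would on its usual reading give standard errors about 20% too small at the planned loss, and every missing-data method named rests on missing at random

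*Protocol article*

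**What the plan says.** The Data analysis section of the protocol article sets the primary analysis as available-case: "the primary analysis will be performed based on participants with available 8 month primary outcome data". It then names the sensitivity methods twice. One sentence says that "missing data will be imputed through a variety of methods including: regression and multiple imputation as part of a sensitivity analysis". A later one says "Sensitivity analysis on the primary outcome will include multiple imputation using chained equations and regression imputation". Both times regression imputation stands beside multiple imputation as a method of its own. Neither sentence says how its standard error will be obtained.

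The Sample size section plans for a loss to follow-up of at least 20%.

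Two other sections describe how outcomes may come to be missing. Under Ethical issues, a participant who has lost capacity may leave on a consultee's advice: "If the consultee advises that the participant would wish to be withdrawn, the researchers will withdraw them from the study". The same section lets a health professional or site investigator recommend withdrawal, and gives observed mental or physical deterioration as an example of a safety concern. Under Intervention dropout and study withdrawal, data collection stops once a participant has fully withdrawn.

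**The concern.** There are two linked issues.

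- **False precision.** A filled-in value carries no new information about the outcome. If it is analysed as observed, the model counts people whose outcome was never seen and also underestimates the residual variance. The interval narrows for no good reason, and a borderline or null primary result could appear significant in the check meant to test it.
- **A shared assumption.** Available-case analysis, chained-equation multiple imputation as usually run, and regression imputation all take missing outcomes to be predictable from what was observed. In a progressive disease, withdrawal after lost capacity or deterioration may depend on the 8-month DEMQOL that was not observed. Agreement among these three methods would say little about that possibility.

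**Working it through.** **Inputs from the Sample size section.** The target is "90% power of detecting this 4 point difference", judged "statistically significant at 5% (two sided) level"; "Assuming a SD of 11 points for the DEMQOL"; "an average cluster size of 8 people with dementia per facilitated group and an intracluster correlation of 0.03"; loss of at least 20%; 1:1 allocation.

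**1. The plan's own figure.**
- Two-sample calculation with difference 4 and SD 11: 159 per arm by the normal approximation; 159.9, so 160, by the t distribution.
- Design effect: 1 + (8 − 1) × 0.03 = 1.21, and 160 × 1.21 = 193.6, so 194.
- Loss: 194 / 0.80 = 242.5, so 243 per arm and 486 in total. The stated sample size reproduces.

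**2. Regression imputation in closed form.** Let m be the missing share, and let values be filled once from the covariates of the analysis model.
- Filled values lie on the fitted line. The residual sum of squares is unchanged but is divided by a larger N, so the residual variance falls by the factor (1 − m).
- The apparent N rises by 1/(1 − m), so the variance of the coefficient falls by a further (1 − m).
- Reported SE / true SE = √[(1 − m)²] = 1 − m = 0.80 at m = 0.20.
- Actual type I error = 2[1 − Φ(1.96 × 0.80)] = 2[1 − Φ(1.568)] = 11.7%.

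**3. Simulation.** 10,000 trials per setting, 243 per arm, SD 11, no true effect, values missing completely at random, clustering and site ignored. The article gives no correlation between baseline and 8-month DEMQOL, so 0, 0.5 and 0.7 are assumed.

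| Missing | Correlation | SE ratio | Type I, imputed | Type I, available cases |
|---|---|---|---|---|
| 20% | 0 | 0.80 | 11.6% | 5.0% |
| 20% | 0.5 | 0.80 | 12.1% | 4.9% |
| 20% | 0.7 | 0.80 | 11.5% | 5.2% |
| 20%, random residual added | 0.5 | 0.83 | 10.6% | 5.3% |
| 10% | 0.5 | 0.89 | 8.1% | 5.6% |
| 30% | 0.5 | 0.70 | 17.4% | 5.4% |

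Without the added residual, the imputed point estimate is identical to the available-case estimate.

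**4. What this could look like.** The design SE is 11 × √(2 × 1.21 / 194) = 1.23. An observed difference of 2.0 gives z = 1.63 and p of about 0.10. With the SE shrunk to 0.80 × 1.23 = 0.98, z = 2.04 and p is about 0.04. This applies the unclustered ratio of 0.80 to a clustered SE, so it is illustrative.

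**5. Departure from missing at random.** Let m1 and m0 be the missing shares in the JtD and control arms, and d1 and d0 the points by which the missing means fall below their prediction. A missing-at-random estimate of the difference is biased by m1·d1 − m0·d0. The departures and splits below are assumptions.
- 20% missing in each arm, equal departure: bias 0.
- 25% v 15% missing, departure 5.5 or 11 in both arms: 0.10 × 5.5 = 0.55, or 0.10 × 11 = 1.1.
- 20% missing in each arm, departure in the JtD arm only: 0.2d, which is 0.8 at d = 4, 1.1 at 5.5 and 2.2 at 11, against a target of 4.

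**6. Tipping point,** with the SE held at 1.23, 20% missing per arm and the departure in the JtD arm only. An observed difference of 4 has a lower limit of 4 − 1.96 × 1.23 = 1.59, so significance is lost at 1.59 / 0.20 = about 8 points. An observed difference of 3 has a lower limit of about 0.59, and loses it at about 3 points.

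**The case against.** The strongest reply on regression imputation is that the article states neither single filling nor a naive variance, so a corrected one such as the bootstrap is not excluded. The result would also be only a supporting analysis with no decision rule attached, reported beside multiple imputation. Both points are correct. They limit the consequence, but the ordinary meaning of the term still yields wrong error bars, and the article names the method twice.

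The reply on informative dropout has more force, and three stronger readings should be resisted.

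- A reader might infer that no analysis will relax missing at random. The article does not support that: both lists of methods are open-ended, and the statistical analysis plan is not at hand. Only the named methods can be judged.
- A reader might infer that the protocol itself causes deterioration-related loss. Disease progression drives it, and the article works against it. People who leave only the intervention are still followed; second visits and telephone collection giving priority to DEMQOL are offered; and participants who lose capacity may stay with fewer measures or prompts. It is also unclear whether a recommended withdrawal means leaving the intervention or the study.
- A reader might infer that such dropout must bias the comparison. It does so only if the missing share or the departure differs by arm, and the withdrawal routes apply to both arms.

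It is also fair to say that chained equations can draw on further variables such as PHQ-9 or GAD-7, which weakens the assumption. It remains a missing-at-random assumption.

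**Conclusion.** The point holds for regression imputation on its usual reading. At 20% missing, the SE is understated by about 20% and a nominal 5% test runs at about 11-12%, rising to about 17% at 30% missing. This rests on values filled once and analysed as observed, on data missing completely at random, and on ignoring clustering. That the point estimate stays the same holds when the imputation and analysis models share covariates.

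A reader might take the 11-12% as the trial's error rate. It is not: the primary test uses available cases and stays near 5% in the same simulations, and the sample size is untouched.

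On informative dropout the conclusion is narrower. The methods named share one assumption that the article's own withdrawal routes give reason to probe. The possible bias runs from zero, with equal shares and departures, to 0.2d when only one arm departs.

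**What to change.** - Drop regression imputation as a sensitivity analysis of the primary outcome, or state a valid variance for it, for example by bootstrap.
- Keep multiple imputation by chained equations, and state that it assumes missing at random.
- Make a delta-adjusted (tipping-point) multiple imputation the second check. Shift imputed DEMQOL by a prespecified range in each arm separately, and report the shift at which the conclusion changes. A range reaching about 8 points would cover the illustration above. Shifting both arms equally is not enough, because it moves nothing when the missing shares are equal.
- Report reasons for withdrawal by arm, including withdrawals on consultee advice, so that readers can judge which shifts are plausible.

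The cost is a change of wording and a few extra analysis runs. No new data are needed, and the primary analysis and sample size stay as they are.
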